#### 3.4.2. Microvascular Function Assessment

Upon assent, a full coronary microcirculation assessment will be performed using guidewire-based technology (PressureWire™ X Guidewire, Abbott, IL, USA) and the thermodilution method in the culprit vessel, as previously described [11,12,13]. Following an intra-coronary bolus of 200–300 µg of isosorbide dinitrate, the guidewire will be calibrated and equalised before advancing toward the third segment of the infarct-related artery. Baseline parameters of microvascular function will be recorded, including mean aortic pressure (Pa), mean distal pressure (Pd), and mean transit time (mTt). The latter will be calculated as the average transit time measurement from three separate intracoronary injections of 3 mL of room temperature 0.9% saline solution. Hyperaemia will be induced by administering an intravenous infusion of adenosine at a rate of 180 µg/kg/min for at least two minutes. A repeat measurement of Pa and Pd will be recorded, as well as mTt at stress. This will be calculated using three separate intra-coronary injections of 3 mL of room temperature 0.9% saline solution. Fractional flow reserve (FFR), coronary flow reserve (CFR), and IMR using the current equations and reported instantaneously by the site study team (Figure 2):

FFR = Pd/Pa (during hyperemia)

CFR = mTt_baseline_/mTt_hyperemia_

IMR = Pd × mTt (during hyperemia)

#### 3.4.3. Randomisation

The SECURE study will only randomise participants who have preserved microvascular function as defined by IMR ≤ 40. Based on previous studies [7,14], we expect that two-thirds of patients with good procedural outcomes, including TIMI 3 flow, will have preserved microvascular function as defined by the SECURE study methodology.

Once microvascular function assessment is performed, patients with IMR ≤ 40 will be 1:1 randomised by means of a web-based randomisation secure method with no stratification block. Blinding or masking of the randomisation group cannot be applied, given the nature of the study. Therefore, patients as well as physicians will be aware of the discharge strategy; however, the analysis of the primary endpoint of left ventricular function will be blindly performed.

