### 3.6. Statistical Analysis

The obtained data will be assessed for normality distribution and reported as means (and standard deviation) or medians (and inter-quartile range) accordingly. The primary endpoint of left ventricle ejection fraction will be compared according to the in-hospital LOS groups using an unpaired *t-test* (or Mann–Whitney U test if appropriate). Other cardiac MRI endpoints, such as left ventricle volume and infarct size, will be evaluated using standard statistical tests depending on whether the data will be normally distributed or skewed. The composite clinical endpoints will be assessed with the use of cumulative incidence curves and the estimated Cox proportional hazards model. Each component of the clinical endpoints will be similarly compared between the two groups using chi-square or Fisher’s exact test, as appropriate.

The study is designed to establish the non-inferiority of early discharge compared to standard practice on left ventricle function at three months following STEMI presentation in patients with preserved microvascular function. Previous data suggested that left ventricle ejection fraction was 46 ± 8% in patients presenting with STEMI who underwent an uncomplicated procedure with final TIMI 3 flow and were hemodynamically stable post PPCI [16,17]. Assuming a non-inferiority margin of 5% difference in left ventricle ejection fraction with 80% power at an alpha level of 0.025, a sample size of 82 patients is required (41 patients in each group). An absolute difference of 5% in LVEF was selected based on prior studies, whereas differences in this magnitude are generally considered within the range of measurement variability and unlikely to translate into meaningful differences in clinical outcomes, particularly in haemodynamically stable, low-risk patients [16,18]. Given that 25% of patients presenting with STEMI and TIMI 3 flow will have IMR > 40 [19], and assuming that 5% of included patients will be lost to follow-up, the total sample size is estimated as 122 patients. The primary analysis will be conducted according to the intention-to-treat principle, but per-protocol analysis will also be performed. Missing CMR data will be handled using predefined sensitivity analyses.

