IMR provides a robust measure of microvascular integrity and has shown excellent ability in predicting the recovery of left ventricle function [5]. It has also been linked to clinical outcomes, and major clinical adverse events were significantly higher in patients with IMR > 40 compared to those with IMR ≤ 40 (17.1% vs. 6.6%, *p* = 0.027) [10]. In fact, IMR > 40 was associated with more than a 4-fold increase in risk of death and heart failure at one year [7,23]. Importantly, IMR exists as a continuum, and a pooled analysis of 1265 patients from 6 cohorts highlighted that serious adverse clinical events such as cardiac death can be predicted using a higher IMR cutoff (above 70) in patients presenting with STEMI [24]. Nonetheless, the same study highlighted that IMR above 40 was associated with more cardiac death, a higher composite of cardiac death and heart failure, a larger infarct size and more frequent microvascular obstruction and intra-myocardial haemorrhage [24]. Whilst dichotomisation may reduce granularity, the selected binary threshold was chosen to enhance clinical interpretability and real-world applicability of the discharge strategy.

The randomisation process within the SECURE study is planned without any stratification. An imbalance between treatment groups may be prevented using stratification for known factors that influence prognosis [25]. There are several clinical and angiographic features that are considered key prognostic variables in patients presenting with STEMI; however, their interaction with the short length of stay is yet to be determined. Overall, IMR may serve as a useful tool to identify patients who may be at low risk of early adverse events and potentially suitable for early discharge from the hospital.

In a previous study that included 261 patients who underwent PPCI, the incidence of cardiac complications before hospital discharge or within 30 days, defined as the composite of cardiac death, cardiogenic shock, pulmonary oedema, malignant arrhythmias, cardiac rupture, and presence of left ventricular thrombus, was 8.4% (22 out of 261). IMR ≤ 40 was recorded in all patients without in-hospital complications [7]. On the other hand, 1 in 7 patients with IMR > 40 was associated with in-hospital adverse events [7]. It had a sensitivity of 100% with a negative predictive value of 100% and outperformed existing criteria for early discharge, such as PAM-II and the Zwolle scores [7].

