**Figure 2 jpm-16-00207-f002:**
[figure not shown]
An illustrative example of coronary microcirculation assessment using PressureWire™ X. The top row represents a patient with preserved microcirculation function (IMR less than 40), and the bottom row illustrates a patient with impaired microcirculation assessment (IMR above 40). Blue curves show resting transit times and orange shows hyperaemic transit times. Resting as well as hyperaemic pressure and flow indices are displayed on the right side of the Figure.

**Table 1 jpm-16-00207-t001:** Inclusion and exclusion criteria of the SECURE study.

Inclusion criteria
Age 18–90 years
Successful revascularisation with TIMI 3 flow
Haemodynamic stability following PPCI Preserved microvascular function, defined as IMR ≤ 40
Ability to provide verbal consent
Exclusion criteria
Out-of-hospital cardiac arrest
Suboptimal angiographic results
Previous coronary artery bypass grafting
Cardiogenic shock or pulmonary oedema
Planned staged PCI during index admission
Known contraindication to adenosine
Known contraindication for CMR
Pregnancy or breastfeeding

**Table 2 jpm-16-00207-t002:** Primary and secondary objectives of the SECURE study.

Objectives	Outcome Measures	Evaluation Timepoints
Primary Objective Impact of early discharge on left ventricle function in STEMI patients with preserved microvascular function	Left ventricle ejection fraction as estimated on CMR	3 months
Secondary Objectives (a) Safety of early discharge strategy	The composite of all-cause mortality, recurrent myocardial infarction, unplanned revascularisation, readmission with heart failure, cardiac arrest, sustained ventricular tachycardia/fibrillation, and cardioverter defibrillator implantation.	3 and 12 months.
(b) Cost-effectiveness	The potential cost-saving of using coronary physiology to guide early hospital discharge in patients presenting with STEMI and preserved microvascular function.	3 months
(c) Impact on functional status	The severity of angina symptoms and functional status in STEMI patients with preserved microvascular function according to their hospital discharge policy	3 months

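### The primary LVEF comparison is fixed as unadjusted although prognostic data are known before randomisation: the test is valid, but precision is lost

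*Protocol article*

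**What the plan says.** Section 3.4.3 of the protocol article describes allocation as "1:1 randomised by means of a web-based randomisation secure method with no stratification block". Section 3.6 names the primary test: "The primary endpoint of left ventricle ejection fraction will be compared according to the in-hospital LOS groups using an unpaired" t-test, with a Mann–Whitney U test as the alternative. It mentions no covariates. The outcome in Table 2 is "Left ventricle ejection fraction as estimated on CMR" at 3 months, and Section 3.4.6 describes CMR at three months only, so no baseline CMR value is planned.

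The Discussion accepts that stratifying on known prognostic factors may prevent imbalance and that STEMI has such factors. It then sets this aside because "their interaction with the short length of stay is yet to be determined". The same section says that IMR has "shown excellent ability in predicting the recovery of left ventricle function". IMR is measured before every randomisation (Sections 3.4.2 and 3.4.3). The culprit vessel and the flow at presentation are seen during the PPCI.

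**The concern.** Whether to stratify on a factor, or adjust for it, depends on how strongly the factor is associated with the outcome. No interaction with treatment needs to be known. The Discussion's reason therefore confuses prognosis with effect modification.

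The document itself treats infarct extent as a driver of LVEF. Section 3.1 requires a large culprit vessel because small infarcts would dilute an effect. It nevertheless admits patients whatever their flow at presentation, and Table 1 does not restrict infarct location. Some prognostic spread therefore remains within each arm. An unadjusted comparison leaves it in the error term, in a trial planned at 80% power with 41 patients per arm. What is at stake is the width of the confidence interval that will be set against the 5-point margin.

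**Working it through.** **Inputs from the document (Section 3.6).** SD 8: "Previous data suggested that left ventricle ejection fraction was 46 ± 8% in patients presenting with STEMI". Margin, power and alpha: "Assuming a non-inferiority margin of 5% difference in left ventricle ejection fraction with 80% power at an alpha level of 0.025". Sample size 82, or 41 per arm. Alpha is read as one-sided.

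**Inputs assumed, because the document gives none.** Share of LVEF variance explained by the covariates (R²): 10% to 30%. For the imbalance example: a binary factor present in 45% of patients that lowers LVEF by 4 to 8 points.

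**1. The plan's own figure.** n per arm = 2 × [8 × (1.960 + 0.842) / 5]² = 40.2, rounded up to 41, so 82 in total. The stated figure reproduces. It rests on the full, unadjusted SD of 8, so design and analysis agree with each other.

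**2. Precision without adjustment.** Standard error = 8 × √(2/41) = 1.77 points. The 95% half-width is 1.96 × 1.77 = 3.46 points. Power from the noncentral t distribution is 79.8%.

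**3. Precision with adjustment.** Residual SD = 8 × √(1 − R²).

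| R² (assumed) | Residual SD | Power at 41 per arm |
|---|---|---|
| 0 (unadjusted) | 8.00 | 79.8% |
| 10% | 7.59 | 83.8% |
| 20% | 7.16 | 87.8% |
| 30% | 6.69 | 91.6% |

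**4. If the covariates are uninformative.** In simulation (20,000 trials per setting, 41 per arm), one covariate unrelated to LVEF gave power of 79.8% adjusted against 80.0% unadjusted. With k such covariates and N = 82, the variance is inflated on average by (N − 3)/(N − k − 3). For k = 3 this is 79/76 = 1.04, which raises the standard error by about 2%, to 1.80 points, and lowers power by between one and two percentage points. The table does not include this small cost, so its gains are slightly generous.

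**5. Type I error.** In the same simulations, with the true difference set at the margin, the one-sided error rate was 0.024 to 0.026 both with and without adjustment.

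**6. Size of a chance imbalance.** The between-arm difference in the share of patients with a 45%-prevalence factor has SD √(2 × 0.45 × 0.55 / 41) = 0.11. A difference of at least 15 points arises in about 15% of trials. At 15 points the unadjusted contrast shifts by 0.15 × 4 = 0.6 to 0.15 × 8 = 1.2 points, which is 12% to 24% of the margin and less than one standard error (1.77). A difference of at least 20 points arises in about 6% of trials and would shift the contrast by 0.8 to 1.6 points.

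**The case against.** The strongest reply is that nothing here is wrong in the sense of invalid. A t-test after simple 1:1 randomisation controls its error rate, and the sample size was calculated for exactly that test. This stands.

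A reader might infer that a chance excess of large infarcts in one arm would bias the result and go unaccounted for. The document does not support that. The SD of 8 is the total between-patient SD, so it already contains the variation due to infarct location and severity. The shifts in step 6 are part of the uncertainty that the confidence interval reports; they do not come on top of it. Adjustment would also deal only with factors that are measured and reasonably modelled.

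A reader might also infer that the plan rejected adjustment for a mistaken reason. The Discussion's argument concerns stratification only; no reason is given for leaving the analysis unadjusted.

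The size of the gain is open to challenge, and this stands too. R² is assumed. The statement that IMR predicts recovery is not confined to low values, whereas only patients at or below 40 are randomised, and that truncation weakens IMR as a covariate. The requirements for a large culprit, TIMI 3 flow and haemodynamic stability narrow the prognostic spread further.

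Data availability has limits as well. Troponin and ECG are recorded only after written consent (Section 3.4.4), symptom-to-reperfusion time is not named as collected, and the article does not say that presenting flow will be recorded. A statistical analysis plan that is not shown could add an adjusted model, but this document already names the primary test.

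**Conclusion.** The point holds as one about efficiency. The primary test is fixed as unadjusted after unstratified randomisation, although IMR and the culprit vessel are known for every randomised patient before allocation. The comparison is valid and 82 patients suffice for it on the stated inputs. Adjustment would raise power from about 80% to between 84% and 92% if the covariates explain 10% to 30% of LVEF variance. That range is an assumption, and truncation of IMR at 40 argues against relying on IMR alone to deliver it. If the covariates explain nothing, the cost is at most a point or two of power.

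The Discussion's sentence on interaction is a wrong reason for not stratifying and should be corrected. It does not undermine the validity of the trial.

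**What to change.** Before any outcome data are seen, prespecify the primary estimate as an ANCOVA of 3-month LVEF on arm with a short list of pre-randomisation covariates: culprit vessel (LAD versus other), IMR as a continuous value and, if it is recorded, TIMI flow at presentation. Declare non-inferiority if the lower limit of the adjusted 95% confidence interval for early minus standard discharge lies above -5 points. Keep the unadjusted comparison as a sensitivity analysis. Do not adjust for anything measured after randomisation, such as peak troponin or in-hospital echocardiography, because its timing or value may depend on the arm.

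Reword the Discussion to say that stratification or adjustment is justified by a factor's association with LVEF, whether or not it interacts with length of stay.

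The cost is wording in the analysis plan, one sentence in the Discussion, and a check that the chosen covariates are captured for every patient. The randomisation system and the sample size need not change.

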#### 3.4.4. Full Informed Consent and Baseline Data Collection

Following the completion of the PPCI, full written consent will be sought from the patient. Given the nature of the study and the randomisation process, it will be recommended to approach the patient as soon as practical to do so. This will allow the patient to read, reflect and ask any questions related to the study and its procedure.

Upon obtaining a written consent form, baseline clinical data will be recorded. This will include medical history, including the patient’s demographic, procedural and medication details. Routine laboratory blood results, including cardiac troponin level and 12-lead electrocardiogram, will also be recorded.

Patients will undergo standard in-hospital management, including cardiac monitoring, echocardiography, optimisation of medical therapy, and ongoing education.

#### 3.4.5. Clinical Follow-Up

A 24 h telephone clinic follow-up will be scheduled for patients with low IMR (≤40) who are randomised into the early discharge group. Patients in this group will be contacted the following day to ensure well-being and ongoing education regarding diagnosis and future management. This visit will also be used as an opportunity to optimise medical therapy. Introducing medications following STEMI presentation is not universally standardised, and titration does not follow a specific protocol; therefore, this will be decided by the same study team to minimise confounders and ensure consistency in the management of their medications. It will also be used to ensure that the patient has a good understanding of the current medical treatment, including antiplatelet, lipid-lowering, and other secondary prevention therapies.

At 3 months, patients with low IMR (≤40), irrespective of their discharge strategies, will have a scheduled telephone follow-up to collect data on any medical treatment or clinical adverse events. This will include cardiac and cerebrovascular events, including cardiac and all-cause death. Data on any hospital admission for cardiac or non-cardiac reasons will also be recorded. A full medication list will also be recorded, including doses of cardiovascular secondary preventive therapies. A comparison of medication doses according to the hospital discharge strategy will be performed by standardising current doses of each of the guidelines-recommended preventive treatments. This will be executed by calculating the ratio of current to the maximal dose of each therapy and, subsequently, averaging the results to reflect the current treatment that each patient is receiving at three months. This value will be referred to as the average standardised medical treatment (ASMT) dose.

A second telephone follow-up will be scheduled at 12 months to obtain similar data from patients with low IMR who are assigned to either early discharge or standard in-hospital LOS.

#### 3.4.6. Cardiac Magnetic Resonance Imaging

All patients in the randomised cohort (both experimental and control groups) will be invited to undergo CMR at three months. Standard MRI sequences include real-time cine imaging, and late gadolinium enhancement will be performed. This visit will enable assessment of left ventricle function (primary endpoint), left ventricle volumes, and infarct size (secondary endpoints).

### 3.5. Objectives and Outcome Measures

The study’s objectives and outcome measures are presented in Table 2. The primary objective of the SECURE study is to assess whether an early hospital discharge strategy, i.e., within 24 h, would have any impact on left ventricle recovery as assessed on CMR. This will be evaluated in patients with preserved microvascular function, defined by low IMR, following successful PPCI. One rationale for keeping STEMI patients in the hospital is to optimise medical treatment and emphasise education about the current condition. Therefore, by adopting early hospital discharge, it is plausible that opportunities to titrate medical treatment and ensure compliance may be compromised. This may result in smaller drug doses and subsequently lower left ventricular function that can be detected using CMR.

The secondary objectives of the SECURE study will include providing clinical safety data on using coronary physiology to guide early hospital discharge. Clinical events are collected as secondary and exploratory safety endpoints, and the study is not powered to detect any difference between the two randomised groups. Data on all-cause mortality, recurrent myocardial infarction, unplanned revascularisation, readmission with heart failure, cardiac arrest, sustained ventricular tachycardia/fibrillation, and cardioverter defibrillator implantation will be collected at 3 months as well as 12 months. This is to ensure that the early discharge strategy is not associated with increased clinical adverse events that may be negated by in-hospital optimisation of medical treatment. Additionally, the SECURE study will assess the cost-effectiveness of using coronary physiology assessment for the National Health Service (NHS) to identify a group of patients who are suitable for early hospital discharge. This remains an exploratory analysis, but it will provide important data to assess the health economic benefits from implementing an early discharge strategy in the low-risk population. The intended analysis will evaluate whether any potential cost-saving, by reducing the number of days in coronary care units and cardiology wards, is not offset by using additional guidewires to assess microvascular function or by setting up a nurse-led follow-up clinic following hospital discharge. Importantly, it is recognised that early outpatient follow-up may reduce readmission rate, which was reported to be more than 10% in patients presenting with acute MI [15]. Finally, the SECURE study will evaluate the functional status and severity of angina symptoms according to the hospital discharge strategy.

### 3.6. Statistical Analysis

The obtained data will be assessed for normality distribution and reported as means (and standard deviation) or medians (and inter-quartile range) accordingly. The primary endpoint of left ventricle ejection fraction will be compared according to the in-hospital LOS groups using an unpaired *t-test* (or Mann–Whitney U test if appropriate). Other cardiac MRI endpoints, such as left ventricle volume and infarct size, will be evaluated using standard statistical tests depending on whether the data will be normally distributed or skewed. The composite clinical endpoints will be assessed with the use of cumulative incidence curves and the estimated Cox proportional hazards model. Each component of the clinical endpoints will be similarly compared between the two groups using chi-square or Fisher’s exact test, as appropriate.

The study is designed to establish the non-inferiority of early discharge compared to standard practice on left ventricle function at three months following STEMI presentation in patients with preserved microvascular function. Previous data suggested that left ventricle ejection fraction was 46 ± 8% in patients presenting with STEMI who underwent an uncomplicated procedure with final TIMI 3 flow and were hemodynamically stable post PPCI [16,17]. Assuming a non-inferiority margin of 5% difference in left ventricle ejection fraction with 80% power at an alpha level of 0.025, a sample size of 82 patients is required (41 patients in each group). An absolute difference of 5% in LVEF was selected based on prior studies, whereas differences in this magnitude are generally considered within the range of measurement variability and unlikely to translate into meaningful differences in clinical outcomes, particularly in haemodynamically stable, low-risk patients [16,18]. Given that 25% of patients presenting with STEMI and TIMI 3 flow will have IMR > 40 [19], and assuming that 5% of included patients will be lost to follow-up, the total sample size is estimated as 122 patients. The primary analysis will be conducted according to the intention-to-treat principle, but per-protocol analysis will also be performed. Missing CMR data will be handled using predefined sensitivity analyses.

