## 2. Rationale of the SECURE Study

Identifying low-risk patients presenting with STEMI who underwent successful PPCI and are suitable for early hospital discharge would be beneficial for patients, physicians, and health care providers. It is well-established that patients feel more supported at home and are often more satisfied with short in-hospital LOS, particularly when discharge planning is well-structured and includes short-term follow-up. Similarly, early hospital discharge will increase efficiency and optimise the use of health care resources, including treating more patients within the same bed capacity.

Determining low-risk STEMI patients who are candidates for early hospital discharge remains to be established. IMR is a reproducible and safe measurement that can be calculated using the guidewire-based thermodilution method, which is widely available in coronary catheterisation laboratories [8]. IMR assessment can be performed immediately following PPCI and can provide prognostic information for patients presenting with AMI [9,10]. Therefore, we set out to study the feasibility of using IMR in patients presenting with STEMI who underwent successful PPCI to guide early hospital discharge. A comparison of patients without major microvascular dysfunction, defined as IMR of equal or less than 40 units, is planned according to their hospital discharge strategies. This means comparing patients with low IMR who are assigned to early hospital discharge, i.e., within 24 h, versus standard in-hospital LOS. We expect that patients with early hospital discharge would have similar left ventricular function on CMR at three months, without increased risk of major adverse clinical events, including death, recurrent myocardial infarction, unplanned revascularisation, readmission to hospital with heart failure, or cardiac arrest, sustained ventricular tachycardia/fibrillation, and cardioverter defibrillator implantation.

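### The named primary tests are not tied to the 5-point non-inferiority margin, so in their ordinary form their p-values do not establish non-inferiority

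*Protocol article*

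**What the plan says.** All the key statements are in section 3.6 of the protocol article.

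- **Primary analysis:** "The primary endpoint of left ventricle ejection fraction will be compared according to the in-hospital LOS groups using an unpaired" t-test, with the alternative "or Mann–Whitney U test if appropriate". The choice follows from an assessment of normality.
- **Design aim, in the next paragraph:** "The study is designed to establish the non-inferiority of early discharge compared to standard practice on left ventricle function at three months".
- **Margin and error rate, in the sample-size sentence:** "Assuming a non-inferiority margin of 5% difference in left ventricle ejection fraction with 80% power at an alpha level of 0.025". This leads to 82 patients, 41 per group. The sidedness of the 0.025 is not stated.
- **Justification of the margin:** "An absolute difference of 5% in LVEF was selected based on prior studies". This puts the margin on the absolute scale.

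Elsewhere, section 3.5 words the primary objective as a question about whether early discharge affects left ventricular recovery at all, which is the language of a difference test. Section 4 looks ahead to a conclusion that the strategy is non-inferior. No section gives a confidence interval for the difference, a null hypothesis shifted by the margin, or a success criterion set against -5 points.

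**The concern.** A non-inferiority claim needs the data to exclude a loss as large as the margin. The usual unpaired t-test asks whether the data exclude a difference of zero. These are different hypotheses, and a non-significant answer to the second says little about the first: it can come from a small true loss, or from too little precision to see a large one.

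The fallback is harder to reconcile. The usual Mann–Whitney test compares ranks, and its p-value comes with no mean difference or interval that could be placed beside 5 LVEF points. If the normality check sends the analysis that way, the article does not say how the margin is to be applied.

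At stake is the trial's single primary conclusion. If the article's text were followed literally, the reported p-value would not answer the declared question, and the rule for success could be settled after the results are known.

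**Working it through.** **Inputs.** From section 3.6: margin 5 points absolute, SD 8 ("left ventricle ejection fraction was 46 ± 8"), power 80%, 41 per arm, and "at an alpha level of 0.025". Assumed: a true difference of 0, in line with the expectation in section 2 ("We expect that patients with early hospital discharge would have similar left ventricular function on CMR at three months"), and one-sided use of the 0.025.

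**1. Reproduce the plan's figure.**
n per arm = 2 × SD² × (z for 0.975 + z for 0.80)² / margin² = 2 × 64 × (1.960 + 0.842)² / 25 = 40.2, rounded up to 41, or 82 in total. This matches. One-sided 0.05 would give 32 per arm and two-sided 0.025 would give 49, so one-sided 0.025 is the reading that fits. A two-sided 0.05 superiority test for a 5-point difference also gives 41 per arm, so the sample size alone does not show which hypothesis the test addresses.

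**2. Precision at 41 per arm.**
SE = 8 × √(2/41) = 1.767. The critical t on 80 df is 1.990. The 95% CI half-width is 1.990 × 1.767 = 3.52 points.

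**3. What each rule accepts, with observed SD 8.**
- Ordinary t-test: non-significant when the observed difference lies between about -3.5 and +3.5.
- Margin-based rule: passes when the observed deficit is smaller than 5 − 3.52 = 1.48 points.
- So an observed deficit of about 1.5 to 3.5 points is not significant and yet fails non-inferiority.

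**4. Operating characteristics (noncentral t, 80 df).** The second column matters only if non-significance at two-sided 0.05 is taken as success.

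| True difference (early minus standard) | t-test non-significant | Margin-based rule passes |
|---|---|---|
| 0 | 95.0% | 79.8% |
| -3 | 61.1% | 20.0% |
| -5 (at the margin) | 20.2% | 2.5% |

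At the margin the ratio is 20.2 / 2.5, or about 8.

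**5. How often the two rules part.** By simulation (400,000 runs), the result is non-significant but fails non-inferiority in about 18% of trials at a true difference of 0, 41% at -3 and 18% at -5. The opposite conflict, a significant deficit that still meets the margin, needs a half-width below 2.5 points. It did not occur in the simulation at the planned size and SD.

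**The case against.** The strongest reply is that section 3.6 states no null hypothesis. A t-test with its null moved to -5, or a t-based 95% CI set against -5, is still an unpaired t-test, and 41 per group is the number such a test needs. The article gives the hypothesis, the margin with its justification, alpha, power, an intention-to-treat primary analysis and a per-protocol analysis. It is a condensed account, and the full protocol or SAP may contain the missing sentence.

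Much of this stands, and it rules out several stronger readings:

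- A reader might infer that the named t-test cannot show non-inferiority. It can, once its interval or null is tied to the margin.
- A reader might infer that the Mann–Whitney route leaves the hypothesis wholly untested. A shifted Mann–Whitney test or a Hodges–Lehmann interval could address it, though as a location shift and not a mean difference.
- A reader might take 20% as the plan's error rate. It belongs to a rule that the article does not state; 0.05 is not given as the trial's alpha.
- A reader might take one-sided as a stated property of the alpha. It is inferred from the sample size.

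What does not stand is that this is only detail left for later. The article names a primary test and a fallback, and the ordinary use of both answers a different question from the declared one. The wording of the objective in section 3.5 points the same way. A document that applied the margin would have to add to this text and, for the fallback, say something different.

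**Conclusion.** The point holds as a mismatch between the declared hypothesis and the named analysis. It is not a demonstration that the trial will reach a wrong conclusion. Run in their ordinary form, the tests yield p-values that do not establish non-inferiority, and the Mann–Whitney p-value has no stated link to the 5-point margin.

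The size is conditional. With normal data, 41 evaluable per arm and SD 8, reading two-sided non-significance as success would pass a loss equal to the margin about 20% of the time, against 2.5%. Observed deficits of about 1.5 to 3.5 points are where the two rules disagree. The sample size is not in question: it reproduces. The proof-of-concept label and the larger study called for in section 4 limit the consequences, but the decision rule still governs the only primary conclusion.

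**What to change.** 1. Add a decision rule to section 3.6, for example: *Non-inferiority is concluded if the lower limit of the two-sided 95% confidence interval for the mean difference in 3-month CMR LVEF (early minus standard discharge) lies above -5 percentage points, corresponding to a one-sided alpha of 0.025.*
2. Remove the normality-driven switch to Mann–Whitney for the primary endpoint. If the data are skewed, compare a bootstrap confidence interval for the mean difference with the same -5 limit, so that the quantity estimated does not change.
3. Reword the primary objective in section 3.5 as non-inferiority on LVEF within the 5-point margin.

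If the full protocol or SAP already holds such a rule, bring the published text into line with it. The trial is open-label, so the rule should be fixed before outcomes are compared between arms.

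The cost is wording only. The evaluable sample stays at 82, with power of about 80% at a true difference of 0, and no new data are needed.
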